## Abstract

**Introduction:**

Psychoeducation is a psychosocial intervention aimed at providing knowledge, cognitive and communication strategies to improve illness awareness and coping skills in patients with psychiatric disorders. Adolescence is a critical phase in psychopathological development. Integrating psychoeducational interventions among youngsters, since hospital clinical practice during mental illness onset, can significantly impact on the global functioning and long-term prognosis. This study aims to assess the feasibility and efficacy of a psychoeducational group intervention to reduce emotional dysregulation and affective symptomatology in a sample of youths hospitalized at the Transitional Psychiatry ward, Marche University Hospital, Ancona, Italy.

**Methods:**

Participants (aged 15-24) will attend weekly thematic modules led by psychiatrists, psychologists and trainees. The control group will receive the treatment as usual. The modules included in the intervention will address the following topics: emotions, anxiety, psychotic experiences, addictions, sleep, therapies, communication and social skills. Participants will be assessed at baseline, at the end of the intervention and at 3-, 6- and 12 months post-randomization.

**Results:**

We expect to observe a significant improvement in the emotional regulation and in the secondary outcomes (mental health literacy, internalized stigma, social functioning, rehospitalization, and coping strategies). Satisfaction questionnaires will also be administered at the end of each session to identify any changes to the intervention, adapting it to patient satisfaction.

**Conclusions:**

The protocol proposes a transdiagnostic and multimodal psychoeducational model aimed at a youth population with high clinical complexity, with potential benefits in terms of secondary prevention, therapeutic continuity and reduction of relapses. Intervention from the acute stages of the illness could ensure greater improvement in the subsequent period, while also establishing a stronger therapeutic alliance.

## Introduction

1

The term “psychoeducation” etymologically derives by the Greek word “*psykho*-” (or “*psykhē*”, personified as Psykhē, the beloved of Eros, meaning “*mind*”) and the Latin term “*educationem*” (i.e., “training”) (1). Hence, the “psychoeducation” indicates a specific way of training, information and education about the mental, psychological, cognitive and emotional dimensions, with a specific focus on related attitudes, skills and behaviors (1). Indeed, the historical roots of psychoeducation was dated in the early 18th and 19th century writings of Philippe Pinel (1745-1826), Johann H. Pestalozzi (1746-1827), Jean M. Itard (1774-1838), Samuel G. Howe (1801-1876) and Dorothe Dix (1802-1887). These authors described the use of educational methods to provide therapeutic services and assistance to the physically and mentally disabled patients (1). However, despite these very early contributions, the first use of the word psychoeducation appeared only in 1941 within the chapter entitled “The Psychoeducational Clinic” by Brian E. Tomlinson (2). In the context of childhood and adolescence, modern psychoeducational approaches were developed in response to the problems of juvenile delinquency, which increased as a result of the industrial revolution and large-scale immigration (1). At the forefront, between the mid-1940s and the 1960s, Fritz Redl (1902-1988) and his former student David Wineman (1916-1995) developed the “Life Space Interview”, a series of related strategies to help young people reflect on and learn from important interactions and crises. In 2010, in the first edition of “Psychoeducation in Mental Health,” Walsh defined psychoeducation as a series of individual, family, and group interventions. He specified that these interventions focussed on: a) educating participants about life’s challenges; b) helping participants developing social supports and increasing resources to manage these challenges; and, c) developing coping skills. Interventions should also aim to increase emotional support, reduce participants’ sense of stigma, modify participants’ attitudes and beliefs about their own mental disorder, identify and explore feelings about the problem, develop problem-solving skills, and implement crisis intervention skills (3).

Nowadays, psychoeducation is indeed an umbrella term typically used to capture the basic concepts of providing information to patients, either as part of a therapeutic intervention (e.g., psychoeducation about emotions before introducing a mood meter or behavioral activation techniques as part of the treatment for mood disorders) or as the intervention strategy itself (e.g., group psychoeducation) (4). Providing such tools and information to adolescent patients could help them to promptly identify and properly manage the psychopathological trajectory of a mental condition both in prodromal phase and/or at the very early onset stage, while preventing their clinical course and potentially improving the illness prognosis. Psychoeducation is overly utilized in several settings and clinical contexts such as in the prevention and intervention programs, despite it is universally employed in cognitive-behavioural therapy (CBT) in which it provides information with the aim to increase patients’ knowledge about their presenting mental health issues and diagnosis, eliciting their case formulation, and providing a clear rationale for the treatment approach and implementation, and also by facilitating the normalization, alliance-building, demystification process as well as facilitating the treatment engagement and adherence (5–9). Therefore, psychoeducation could potentially reduce negative feelings related to mental health disorders, such as internalized stigma, feelings of shame, and increase the sense of possibility (including hope, optimism, and relief) which can hinder treatment implementation (5, 7).

Despite the growing interest in the application of psychoeducation in adolescents and young people, the available scientific literature is still limited and fragmented. This lack of evidence makes it difficult to define solid and validated guidelines for the use of psychoeducation with adolescents, especially in more complex contexts such as acute psychiatric settings. Within this context, it has been already suggested the need to develop an age-sensitive psychoeducational intervention, able to adequately address specific adolescents’ developmental needs, by promoting a greater emotional awareness, as well as encouraging adherence to treatment pathways (10–14). Therefore, the primary aim of the present study protocol was to assess the feasibility and the efficacy of a pilot psychoeducational group intervention in a sample of adolescents and young adults with a diagnosis of emotional and/or affective disorders hospitalized within our Transition Psychiatry acute psychiatric ward, in terms of reduction of dysregulated emotional and affective symptomatology in the post-intervention and in the follow-up period. The feasibility will be assessed considering recruitment and retention rates and acceptability of the intervention, while the efficacy will be evaluated through the evaluation of emotional dysregulation pre- and post-intervention. Secondary outcomes included the evaluation of the efficacy of the intervention on the following dimensions: a) improvement of mental health literacy; b) reduction of internalized stigma; c) improvement of psychosocial functioning; d) reduction of relapses and hospitalizations during the 12-months follow-up period; e) improvement of coping strategies and expressed emotions.

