Patients referred to the inpatient Transition Psychiatry unit will be invited to participate in the study if they meet the following inclusion criteria: a) diagnosis of an emotional and/or affective Disorder (i.e., Major Depressive Disorder, Bipolar Disorder, Cyclothymia, Persistent Depressive Disorder, Seasonal Affective Disorder, Disruptive Mood Dysregulation Disorder, Other Specified Depressive Disorder, Unspecified Depressive Disorder, Other Specified Bipolar and Related Disorder, Unspecified Bipolar and Related Disorder, Unspecified Mood Disorder, Oppositional Defiant Disorder, Intermittent Explosive Disorder, Conduct Disorder, Other Specified Disruptive, Impulse-Control, and Conduct Disorder, Unspecified Disruptive, Impulse-Control, and Conduct Disorder) according to the Diagnostic and Statistical Manual of Mental Disorders, Fifth Edition text revised (DSM-5-TR) (15); b) aged 15–24 years old; c) admitted to the acute unit of Transition Psychiatry and expressed the willingness to participate to all the psychoeducational program also in the post-discharge sessions; d) agreement to the study participation during the 12-months follow-up period; e) ability to provide written informed consent (their parents in case they are less than 18 years old). This broad inclusion strategy was adopted to reflect the heterogeneous and often overlapping nature of early psychopathological manifestations during the transition age. In particular, the use of DSM-5-TR diagnoses should consider a dimensional and transdiagnostic framework, because symptom presentations in youths frequently evolve over time and may not yet conform to stable categorical boundaries. Anyways, if a patient is admitted to our department without a prior diagnosis, study inclusion is based on the preliminary diagnosis formulated at admission to our ward. Exclusion criteria will include: a) presence of an intellectual disability and/or mental retardation and/or difficulty in understanding Italian language and/or learning and/or moderate-to-severe cognitive deficits (absolute contraindication); b) patients with current uncontrollable psychomotor agitation and/or current drug and/or alcohol intoxication which may interfere with attention and/or concentration during the psychoeducational sessions (relative contraindication); c) the presence of an acute psychiatric symptomatology which may impact the level of consciousness and/or induce a temporary alteration of cognitive ability (relative contraindication). All included participants will continue to receive the treatments usually provided (e.g., regular psychiatric visits, pharmacological treatments, and psychotherapy). The study will be carried out in accordance with globally accepted standards of good practice and in agreement with the Declaration of Helsinki and with local regulations. An informed consent form will be signed by their parents after full description of study protocol. The study investigators will ensure that all mental health professionals involved in the study are qualified and informed about the protocol, interventions, and trial-related duties. An ethical approval request has been submitted (ID study: 4696) to our local Institutional Ethical Committee of Marche Region and will be obtained before starting with the recruitment.

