## Statistical analysis

5

Sample size has been calculated using the Statistical Software G*Power version 3.1. (Franz, Universitat Kiel, Germany). Based on the primary objective of the study, in order to detect any difference in the mean scores of the subscales of the DERS between the control and the experimental groups, by keeping a statistical power of 0.95 to identify an effect size of 0.8 (α=0.05, two-tailed) and taking into consideration all variables to be entered in the t-test. A total sample size of 84 was established to be reached for the present study (42 participants for each group). Considering the longitudinal follow-up and the clinical instability of the study population, attrition and missing data are expected. Analyses will be conducted on available data, with attrition rates systematically reported. Given the pilot nature of the trial, results will be interpreted with a focus on feasibility and preliminary efficacy. The IBM Statistical Package for Social Sciences software, version 26 (SPSS, Chicago, Illinois, USA), will be used for the data analysis. Descriptive analyses will be performed to describe the socio-demographic characteristics of the sample and to assess the normality of the data. Categorical variables will be summarized as frequency (n) and percentage (%), while continuous variables will be summarized as mean and standard deviation (SD). Categorical variables will also be compared using the χ^2^-test and *post-hoc* tests. To summarize the data and test the differences based on categorical analysis, parametric tests (t-test or ANOVA) or non-parametric tests (Kruskal-Wallis test or Mann-Whitney U test) will be used, depending on the normality of the data. To compare longitudinal data, the paired t-test or Wilcoxon test will be used, again based on normality. Finally, correlation and regression analyses (univariate/multivariate, linear/logistic) will be conducted, including socio-demographic and clinical variables and the total scores and subscales of the various scales, to explore any relationships between the different factors. The statistical significance cut-off will be set at p <0.05.

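### The efficacy definition and the longitudinal test are within-patient, while the sample size and the design rest on a between-arm comparison; the protocol should name one between-arm efficacy test

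*Protocol article*

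**What the plan says.** Several places in the protocol article bear on the efficacy comparison.

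- **Introduction, aims.** After feasibility, the article states that "the efficacy will be evaluated through the evaluation of emotional dysregulation pre- and post-intervention". No arm is mentioned in that definition. The aim covers both the post-intervention assessment and the follow-up period.
- **Statistical analysis, sample size.** The trial is sized, by reference to its primary objective, "in order to detect any difference in the mean scores of the subscales of the DERS between the control and the experimental groups". The inputs are a standardised effect of 0.8, a power of 0.95 and a two-sided alpha of 0.05. A t-test is named, and the result is 84 patients, 42 per arm.
- **Statistical analysis, methods.** "To compare longitudinal data, the paired t-test or Wilcoxon test will be used, again based on normality". Separately, t-test or ANOVA and Mann-Whitney or Kruskal-Wallis tests are listed for group differences, without saying which groups, outcome or visit. Correlation and regression analyses are described as exploring relationships.
- **Abstract, Results.** "We expect to observe a significant improvement in the emotional regulation and in the secondary outcomes". The sentence makes no comparison with control.
- **Methods.** Allocation is randomised 1:1, and "All included participants will continue to receive the treatments usually provided".
- **Discussion.** The control comparison is said to show whether the programme adds anything beyond general health information.

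**The concern.** A paired test compares each patient with his or her own baseline. It has no term for arm, so it cannot separate the programme from anything else that changes between T0 and T1.

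Here much else may change. Patients enter during an acute admission, usual treatment continues in both arms, and controls receive their own educational sessions, including stress management and sleep. DERS may therefore fall in both arms through recovery, concurrent treatment and regression to the mean. Only the randomised contrast removes that shared fall.

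A reader who matches the stated definition of efficacy to the test stated for longitudinal data arrives at the paired test. A significant fall in the experimental arm could then be reported as efficacy, and so could a significant fall there alongside a non-significant one in the control arm. Neither is evidence that the arms differ. Efficacy is part of the primary aim, so the main conclusion is what is exposed.

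**Working it through.** **Step 1. Which comparison produced 84?**

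Inputs from the Statistical analysis section: standardised effect d = 0.8, two-sided alpha 0.05, power 0.95, equal arms.

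Two-sample t-test: noncentrality = d × √(n/2), degrees of freedom 2n − 2.

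- n = 41 per arm: 0.8 × √20.5 = 3.622, power 0.947.
- n = 42 per arm: 0.8 × √21 = 3.666, power 0.952.

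The smallest n reaching 0.95 is 42 per arm, so N = 84, an exact match. A paired t-test at a standardised change of 0.8 would need only 23 patients in all. The stated size comes from a between-arm test.

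**Step 2. What would a paired test show if the programme did nothing?**

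The documents give neither the size of recovery nor the T0–T1 correlation of DERS. Both are assumptions here: a fall m of 0.2 to 0.8 SD, equal in both arms, and a correlation r of 0.3 to 0.7. There are 42 patients per arm with no dropout.

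Standardised paired change: dz = m / √(2(1 − r)). Noncentrality = dz × √42, degrees of freedom 41.

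Three worked cases:

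- m = 0.2, r = 0.3: dz = 0.2/√1.4 = 0.169; noncentrality 1.10; P(significant) = 0.188.
- m = 0.5, r = 0.5: dz = 0.5/√1.0 = 0.5; noncentrality 3.24; P(significant) = 0.886.
- m = 0.8, r = 0.7: dz = 0.8/√0.6 = 1.033; noncentrality 6.69; P(significant) above 0.999.

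The arms are independent and have the same probability p of a significant paired test. The chance of significance in the experimental arm but not in the control arm is therefore p(1 − p).

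| Fall (SD) | r | Experimental arm significant, p | Significant in experimental only, p(1 − p) |
|---|---|---|---|
| 0.2 | 0.3 | 0.188 | 0.153 |
| 0.2 | 0.5 | 0.244 | 0.185 |
| 0.2 | 0.7 | 0.372 | 0.234 |
| 0.3 | 0.3 | 0.361 | 0.231 |
| 0.3 | 0.5 | 0.476 | 0.249 |
| 0.3 | 0.7 | 0.688 | 0.215 |
| 0.5 | 0.3 | 0.762 | 0.181 |
| 0.5 | 0.5 | 0.886 | 0.101 |
| 0.5 | 0.7 | 0.983 | 0.017 |
| 0.8 | 0.3 | 0.990 | 0.010 |
| 0.8 | 0.5 | 0.999 | 0.001 |
| 0.8 | 0.7 | above 0.999 | below 0.001 |

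**Step 3. What would a between-arm test show in the same setting?**

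In 20,000 simulated trials with no programme effect (m = 0.5, r = 0.5), the paired test in the experimental arm was significant in 0.885. The between-arm test was significant in 0.049 on change scores and 0.048 on T1 scores. Both are the nominal 5%, of which half, 2.5%, favours the programme.

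**Step 4. Does the existing size support a between-arm test?**

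Power at 42 per arm for d = 0.8, before attrition:

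- T1 scores, unadjusted: 0.952.
- T1 scores adjusted for baseline, with the SD multiplied by √(1 − r²) and ignoring the one degree of freedom spent on the covariate: 0.967, 0.987 and 0.999 for r = 0.3, 0.5 and 0.7.
- Change scores, with the SD multiplied by √(2(1 − r)): 0.865, 0.952 and 0.997 for the same r.

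Baseline adjustment does not lose power at any of these correlations. Change scores do at r = 0.3.

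**The case against.** The strongest reply is that the article already plans a randomised comparison. The sample-size sentence derives from the primary objective, names a difference between arms and refers to a t-test. The listed group tests could compare arms at any visit. The Discussion gives the comparison with control as the purpose of the design and mentions statistical control for concurrent treatment. The sentence in the aims may say only when DERS is measured, and the abstract is an expectation, not a decision rule. The trial is also a pilot, to be read as preliminary, and a full analysis plan may name the model.

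Much of this stands. A reader might infer that efficacy will be tested only within arms, that randomisation plays no part in the test, or that recovery will be mistaken for benefit. The documents do not support that: no sentence makes a paired test the efficacy criterion, and the sizing points the other way. Nor is it right that follow-up can have no randomised test; none is explicitly assigned to it.

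The mismatch remains. The group tests are not tied to arm, DERS or visit, whereas the definition of efficacy and the longitudinal test are both explicit and both within-patient. An unseen analysis plan could add a between-arm model, but the published definition would then still need correcting. Pilot status does not remove the point, because efficacy is in the primary aim and the trial is sized for it at 0.95 power.

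**Conclusion.** The point holds as an internal inconsistency. The sample size, the randomised design and the stated purpose of the control arm concern a difference between arms, while the efficacy definition and the only named longitudinal test concern change within patients. The text leaves room for recovery under usual care to be reported as a programme effect. That is a risk, not a certainty.

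Its size is conditional on the assumed fall and correlation, and on a within-arm criterion that no passage states. Under those conditions, with no programme effect, the experimental arm's paired test would be significant in about 19% to over 99% of trials. Significance in the experimental arm alone would occur in at most about 25%. That figure is close to the mathematical maximum of p(1 − p) and falls to between 2% and 18% for a 0.5 SD fall. The comparable error for a between-arm test is 2.5%.

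**What to change.** - **Introduction (aims) and Statistical analysis:** state that efficacy is judged by the between-arm difference in DERS at T1, adjusted for baseline DERS, as the single primary comparison. Name the one DERS score this refers to, since the sizing sentence speaks of subscales and Table 3 also describes a total.
- **Follow-up:** treat the between-arm contrasts at T2 to T5 as secondary.
- **Paired tests:** keep them as description of change within each arm, with no efficacy claim attached.
- **Abstract, Results:** reword the expectation as a greater improvement than in the control group.

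Table 2 already schedules DERS at T0 and at every later visit, so no new data are needed. The present size gives power of 0.952 unadjusted, before attrition, for which the article states no rate. The cost is a few sentences and a little more analysis work.

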## Methods

2

A pilot single-centre randomized controlled intervention study was developed to be carried out at the Transition Psychiatry ward (specifically addressed to adolescents and young adults aged 15-24), Unit of Clinical Psychiatry, Department of Neurosciences/DIMSC, University Hospital of Marche Region within the Polytechnic University of Marche, Ancona, Italy. The randomization procedure will be performed using IBM Statistical Package for Social Sciences software, version 26 (SPSS, Chicago, Illinois, USA). For each participant, a random number will be generated using the RV.UNIFORM(0,1) function, which produces values distributed uniformly between 0 and 1. The cases will be then sorted according to the random number obtained and will be assigned to the two experimental groups in a 1:1 ratio. The allocation sequence will be generated by an independent researcher not involved in recruitment or intervention delivery, in order to ensure concealed allocation and minimize possible bias. The entire procedure will be documented to ensure replicability and methodological transparency.

Patients referred to the inpatient Transition Psychiatry unit will be invited to participate in the study if they meet the following inclusion criteria: a) diagnosis of an emotional and/or affective Disorder (i.e., Major Depressive Disorder, Bipolar Disorder, Cyclothymia, Persistent Depressive Disorder, Seasonal Affective Disorder, Disruptive Mood Dysregulation Disorder, Other Specified Depressive Disorder, Unspecified Depressive Disorder, Other Specified Bipolar and Related Disorder, Unspecified Bipolar and Related Disorder, Unspecified Mood Disorder, Oppositional Defiant Disorder, Intermittent Explosive Disorder, Conduct Disorder, Other Specified Disruptive, Impulse-Control, and Conduct Disorder, Unspecified Disruptive, Impulse-Control, and Conduct Disorder) according to the Diagnostic and Statistical Manual of Mental Disorders, Fifth Edition text revised (DSM-5-TR) (15); b) aged 15–24 years old; c) admitted to the acute unit of Transition Psychiatry and expressed the willingness to participate to all the psychoeducational program also in the post-discharge sessions; d) agreement to the study participation during the 12-months follow-up period; e) ability to provide written informed consent (their parents in case they are less than 18 years old). This broad inclusion strategy was adopted to reflect the heterogeneous and often overlapping nature of early psychopathological manifestations during the transition age. In particular, the use of DSM-5-TR diagnoses should consider a dimensional and transdiagnostic framework, because symptom presentations in youths frequently evolve over time and may not yet conform to stable categorical boundaries. Anyways, if a patient is admitted to our department without a prior diagnosis, study inclusion is based on the preliminary diagnosis formulated at admission to our ward. Exclusion criteria will include: a) presence of an intellectual disability and/or mental retardation and/or difficulty in understanding Italian language and/or learning and/or moderate-to-severe cognitive deficits (absolute contraindication); b) patients with current uncontrollable psychomotor agitation and/or current drug and/or alcohol intoxication which may interfere with attention and/or concentration during the psychoeducational sessions (relative contraindication); c) the presence of an acute psychiatric symptomatology which may impact the level of consciousness and/or induce a temporary alteration of cognitive ability (relative contraindication). All included participants will continue to receive the treatments usually provided (e.g., regular psychiatric visits, pharmacological treatments, and psychotherapy). The study will be carried out in accordance with globally accepted standards of good practice and in agreement with the Declaration of Helsinki and with local regulations. An informed consent form will be signed by their parents after full description of study protocol. The study investigators will ensure that all mental health professionals involved in the study are qualified and informed about the protocol, interventions, and trial-related duties. An ethical approval request has been submitted (ID study: 4696) to our local Institutional Ethical Committee of Marche Region and will be obtained before starting with the recruitment.
